# Background

Viral respiratory tract infections (RTIs) are a major burden to public health, causing serious disease especially in the vulnerable population. These infections impose a substantial health burden in all countries. For instance, the World Health Organization (WHO) estimates that there are, annually, 1 billion cases of influenza during interpandemic years alone, with 3-5 million cases of severe illness and 300 000 – 500 000 deaths per year.1

Fear of the global spread of serious respiratory disease persists in light of past pandemics, such as the 2003 SARS coronavirus outbreak, 2009 H1N1 influenza virus, and the recent observation of the Middle East Respiratory Syndrome Coronavirus (MERS CoV), in Gulf countries and elsewhere, with reports of limited person to person transmission.2 Ever-increasing and fast international travel intensifies the risk as well as increases the likelihood of emergence of novel strains of viruses through genetic re-assortment thereby further compounding concern.3

Health authorities require cost-effective interventions that prevent, limit or slow the global transmission of respiratory diseases. Members of the public also require guidance to minimise the spread of infection.

Non-pharmaceutical interventions like personal protective measures such as facemasks and hand hygiene, and population interventions such as social distancing, quarantine and school closures may complement pharmaceutical measures like vaccination (eg, against influenza) and antiviral therapy (eg, anti-influenza drugs) in the prevention and control of viral RTIs. Facemasks could represent a simpler, cheaper alternative (or supplement) to the use of antivirals.

Results from studies examining the effectiveness of facemasks have been either conflicting or inconclusive.4 A randomised controlled trial (RCT) in a household setting found that adherence to facemask use decreased the risk of influenza-like illness (ILI), which was defined as fever and cough or sore throat .5 Two other RCTs found facemasks to be effective in reducing laboratory-confirmed influenza in households but only when implemented together with hand hygiene within 36 hours of a contact developing ILI.6,7 Aeillo and colleagues also found a similar result in the setting of university halls.8 However, three other studies in households did not find facemasks to be effective in reducing ILI.9-11 Surgical masks have been compared with N95 respirators in healthcare settings. Loeb and colleagues found that facemasks were non-inferior to N95, but MacIntyre and colleagues found N95 to be more protective than facemasks against clinical respiratory illness among health care workers.12-14

Meta-analysis of data from 6 trials shows that wearing facemasks is protective against ILI, but do not show that facemasks are protective against laboratory proven influenza (Figure 1).15,7 The major limitation of previous studies is believed to be the small sample size, and resulting lack of power to detect effects of facemasks on laboratory-proven influenza (and other respiratory viruses).15 The largest study so far was a cluster-randomised study in 509 households, with 2788 recruits, conducted by Larson and colleagues, but did not find an additional benefit of facemasks with hand hygiene over health education (regarding preventive measures) on overall rates of laboratory-proven viral infection, although there seemed to be a benefit on secondary transmission of respiratory infection; despite the size of this study, the authors pointed to concerns about under-powering and poor compliance with mask use.10 MacIntyre and colleagues’ individually randomised study with 1669 healthcare workers found no difference in rate of laboratory-proven respiratory pathogens between facemask and N95 arms.14 An observational study at Hajj showed that the use of a facemask by male pilgrims, but not a face-cover by females, was a significant protective factor against ARI while interestingly, a nested case-control study showed that intermittent facemask use was associated with a 2.7 fold greater risk of infection among health care workers at Hajj, suggesting perhaps that a facemask worn in the presence of an infected patient and contaminated with infectious material becomes the source of hand transmission (to the respiratory tract).16,17 Bin Reza *et al*. also consider that failure to reach a firm conclusion may have stemmed from inadequate sample size. 4 They therefore, recommended that sufficient power may be obtained by large multi-centred trials run for several years.4 Such a design at community settings will have considerable logistical and cost issues.

[figure not shown]

**Figure 1:** ***Comparison between mask and control groups in randomised trials*** (adapted from Rashid *et al*. with the inclusion of an additional study7, 15).

We have estimated that about 3500 subjects will be needed in each arm of a study to achieve sufficient power to detect a difference at the level of laboratory-confirmed respiratory viruses (please refer to sample size calculation section). Conducting such a trial at a mass gathering such as the Hajj, where annually about two and half million pilgrims gather from all corners of the world, over two years offers a viable alternative. Thus the logistical difficulties of recruiting a large number of subjects could be reduced. About 30,000 tents are used to house the pilgrims in Mina, a valley on the outskirts of Mecca. Pilgrims stay in these tents for at least 5 days. We would take the advantage of this ‘natural experiment’ to answer an important public health question whether facemasks are effective in preventing respiratory virus infection among Hajj pilgrims. This research is proposed at a time when the emergence of MERS CoV is threatening the world and therefore has an immediate public health implication.2

**Objectives**

*Primary aim*

1. To evaluate the efficacy of facemasks against laboratory-confirmed respiratory viral infections (including influenza, MERS CoV and other respiratory viruses) at Hajj 2013 and 2014.

*Secondary aims*

1. To investigate the transmission pattern of influenza virus at Hajj by studying the genetic relatedness between circulating influenza viruses using deep genomic sequencing.
2. To determine the self-reported influenza vaccine uptake and evaluate its effectiveness at Hajj using a test-negative case-control design.

**Research Plan**

**Design of the trial**

The key steps of the study are shown in Figure 2.

This study will be a large-scale cluster-randomised controlled trial to test the efficacy of facemasks in preventing acute respiratory viral infection including influenza and coronaviruses.

The trial will compare the ‘*use of (simple surgical) facemasks’* versus ‘*no use of facemasks’* among pilgrims during theHajj week (13 to 20 October, 2013, and 2 to 9 October 2014). Randomisation to each arm will be in a 1:1 ratio and will be done according to tents. Computer-generated random numbers will be made by an offsite research coordinator who will not take part in recruitment or assessment of participants. The randomisation will be stratified by gender and country of residence to ensure a balanced and proportionate recruitment.

**Recruitment**

The study will aim to recruit pilgrims at the 2013 Hajj from Saudi Arabia, Qatar and Australia. Whereas in 2014, subjects will also be recruited from Indonesia, Malaysia, Turkey, Morocco, India, Pakistan and Bangladesh (Table 1). Before the commencement of Hajj, the tour groups will be provided with detailed information about the study and encouraged to participate in their respective countries of residence. At Hajj, trained study staff will approach tents for recruitment on the morning or afternoon of the first day of the pilgrim’s stay in Mina (corresponding to13th October, 2013, and 2nd October, 2014). The research team member will explain the study to the assembled pilgrims in each tent and invite them to join the study. If the pilgrims agree to participate, a consent form will be signed and a baseline questionnaire will be filled which will include collecting relevant demographics, vaccination history and clinical information such as respiratory symptoms with duration and pre-existing medical condition (Appendix 1). The participants will be informed whether their tent has been randomised to facemask wearing or no facemask wearing.

­

13th

October

Pilgrims settle into tents

Randomisation

Intervention tents Control tents

All fill baseline questionnaires

Given *Hajj diaries*

Receive masks and demonstration. Do not receive masks

Start wearing masks

14th October

All record symptoms in Hajj diaries

Symptomatic pilgrims are swabbed

Continue mask wearing Do not wear masks

15th October

16th October

Study staff collect *Hajj diaries* in the evening

17th October

18th October

Evening

19th October

Evening

Pilgrims leave Mina and start keeping *post-Hajj* diaries

20th October

No need to keep *post-Hajj* diaries

Mask wearing is no more required No need to avoid mask wearing

Nasal swabs get transported to Sydney

Pilgrims send *post-Hajj* diaries to research physicians

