**Figure 2: Key steps of the study at the Hajj 2013**

**Inclusion criteria**
Pilgrims from participating countries staying in their respective tents
Age ≥18 years.
Informed consent has been agreed and signed.

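### Figure 2 and the text disagree on whether tents are allocated before or after enrolment, and nothing conceals a tent's arm from recruiting staff until consent and baseline are complete

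*Protocol*

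**What the plan says.** The tent is the unit of allocation: "Randomisation to each arm will be in a 1:1 ratio and will be done according to tents" (Protocol, Design of the trial). The same section says: "Computer-generated random numbers will be made by an offsite research coordinator who will not take part in recruitment or assessment of participants".

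Three places bear on the order of steps.

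- **Figure 2.** On the first day the boxes run: "Pilgrims settle into tents", randomisation, intervention and control tents, then "All fill baseline questionnaires". Diaries, and masks for the intervention tents, follow. The figure has no separate consent step.
- **Recruitment, text.** On that same day "trained study staff will approach tents for recruitment on the morning or afternoon of the first day". After the study is explained, "If the pilgrims agree to participate, a consent form will be signed and a baseline questionnaire will be filled". The last sentence of the paragraph is: "The participants will be informed whether their tent has been randomised to facemask wearing or no facemask wearing".
- **Data collection.** For the control arm, this section starts from tents already called no-mask tents, to which no masks are supplied. It then says that their occupants will be enrolled, give consent and complete the baseline questionnaire.

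Entry is individual: "Informed consent has been agreed and signed" (Inclusion criteria). Staff also record how many people were recruited in each tent and how many were in it (Data collection).

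**The concern.** In a cluster trial, randomising the tents protects the comparison of tents. It does not protect the comparison of the people who agree to join within them if those people, or the staff who invite them, already know the arm. Pilgrims who dislike masks may decline in a mask tent. Pilgrims who feel unwell may be more, or less, inclined to join a tent that will receive masks. Staff who know the arm may invite, or apply the mask-contraindication exclusion, differently.

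The eligibility criteria do not exclude pilgrims who already have respiratory symptoms, and a swab follows whenever the daily search finds influenza-like illness. An infection present at entry can therefore become an outcome. The baseline questionnaire asks about respiratory symptoms and their duration, so it is the natural check on this. If it is completed after the arm is known, the answers may be coloured by the arm.

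The Data analysis section specifies intention to treat. That keeps enrolled people in their allocated arm, but it cannot correct a difference in who was enrolled.

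**Working it through.** **Order of steps, set side by side**

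| Step | Figure 2 | Recruitment text | Data collection (control tents) |
|---|---|---|---|
| Tent allocated | Before baseline | Time not stated; done by the time participants are told | Tent already carries its arm label |
| Consent | Not shown | Before participants are told | Described within a labelled tent |
| Baseline questionnaire | After the split into arms | Before participants are told | Described within a labelled tent |
| Arm disclosed to pilgrims | Not shown | Described last | Not stated |
| Arm disclosed to recruiting staff | Not shown | Not stated | Not stated |

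The last row is the gap common to all three. The offsite coordinator settles who makes the sequence. No section says when a tent's arm reaches the staff taking consent.

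**The plan's own sample size (Sample size calculation)**

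Inputs: 12% against 6%, 80% power, 5% significance (two-sided reproduces), intra-cluster correlation 0.10, mean 75 per tent.

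- Design effect: 1 + (75 − 1) × 0.10 = 8.4, as stated.
- Unpooled formula: 7.849 × (0.12 × 0.88 + 0.06 × 0.94) / 0.06² = 7.849 × 0.162 / 0.0036 = 353.2 per arm; × 8.4 = 2967. The pooled-variance version gives 356 × 8.4 = 2990. The stated 2976 lies between the two.
- Loss to follow-up: 2976 × 1.18 = 3512, stated as approximately 3500.

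The sample size reproduces, and this point does not change it.

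**Illustration of what differential enrolment could do**

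Assumption, not in the documents: masks have no effect, and selective enrolment moves the expected event rate in one arm away from 12% by 2 or 3 percentage points.

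- Effective size per arm: 2976 / 8.4 = 354.3.
- SE = √{[p₁(1 − p₁) + p₂(1 − p₂)] / 354.3}; z = |p₁ − p₂| / SE.
- Two-sided rejection = Φ(z − 1.96) + Φ(−z − 1.96).

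| Rates under no mask effect | SE | z | Two-sided false rejection |
|---|---|---|---|
| 14% v 12% (one arm up 2 points) | 0.0253 | 0.79 | 0.124 |
| 15% v 12% (up 3) | 0.0257 | 1.17 | 0.216 |
| 12% v 10% (one arm down 2) | 0.0235 | 0.85 | 0.136 |
| 12% v 9% (down 3) | 0.0230 | 1.30 | 0.256 |

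The nominal rate is 0.05. The same formula returns 0.80 for 12% against 6%, which agrees with the planned power. For scale, 3 points is 0.03 × 75 = 2.25 people per tent of 75, and 2 points is 1.5.

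The direction decides what kind of error results. If extra infected pilgrims join mask tents, almost all the false rejections point to harm from masks. If fewer join, they point to benefit.

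**The case against.** The best defence is the Recruitment text read alone. It gives consent, baseline questionnaire, then disclosure, which is close to the order one would want. A reader might infer from its wording, that the tent has been randomised, that allocation precedes consent. The sentence places randomisation before the informing, not before the consent, so it does not support that inference.

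Two further stronger readings also fail. Figure 2 does not show randomisation before consent, because it has no consent box; it shows it before the baseline questionnaires. And no section says that staff arrive with or without masks in hand; the figure puts mask distribution after baseline.

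It can also be argued that a key-steps diagram is weaker evidence than the paragraph it accompanies, that Data collection may simply be describing the control arm rather than setting a sequence, that tour groups are informed and encouraged before travel so some willingness to join predates allocation, that mask contraindication excludes people in both arms, and that numbers recruited and present are recorded per tent.

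These points limit the risk but do not close the gap. Two places in the protocol do not follow the favourable order. Even that order says only when participants learn the arm, not when staff do. Recorded uptake can reveal unequal participation afterwards, but cannot prevent it or show how those who joined differ. The order of enrolment and concealment is trial conduct that must be settled in the protocol before the first tent is approached, so it cannot be left to a statistical analysis plan.

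**Conclusion.** The point holds as a misalignment plus an omission. Figure 2 and Data collection describe baseline, and in the latter case consent as well, in tents whose arm is already set. The Recruitment text describes consent and baseline before participants learn their arm. Nothing conceals the arm from recruiting staff. If the trial is run as the figure reads, differential enrolment and arm-influenced baseline reports become possible.

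A reader might go further and conclude that the trial is biased, or that its false-positive rate will be 22% or 26%. The documents do not support that: they give no figure for the size or direction of any shift. The range of about 12% to 22% (one arm shifted up) or 14% to 26% (shifted down) rests entirely on an assumed 2 to 3 point shift, with 2976 per arm and design effect 8.4. It shows only that a modest imbalance would matter at this sample size.

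**What to change.** Make Figure 2, Recruitment and Data collection state one order:

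1. The tent is approached and the study explained.
2. All consents and baseline questionnaires in the tent are completed.
3. The numbers enrolled and present are recorded, as Data collection already requires.
4. The allocation is revealed to staff and pilgrims together, by sealed envelope or a call to the offsite coordinator.
5. Masks are issued in intervention tents.

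Add a consent box to Figure 2, and a sentence saying that recruiting staff do not know a tent's arm before step 4. Plan to compare the proportion enrolled of those present, and baseline symptoms, by arm. No rule on later joiners is needed, since the protocol describes recruitment on the first day only.

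Cost: protocol wording, one envelope or call per tent (7000 / 75, about 93 tents over the two years), and a short delay before masks are issued on the first day.

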**Figure 2: Key steps of the study at the Hajj 2013**

**Inclusion criteria**
Pilgrims from participating countries staying in their respective tents
Age ≥18 years.
Informed consent has been agreed and signed.

**Exclusion criteria**
Children aged less than 18 years.
Participation in another clinical trial investigating a medical intervention that may interfere with study outcome measures like proven viral RTI.
Known contraindication to mask use (eg, allergy to surgical mask materials).

Refused to sign a consent form.

**Data collection**

For the tents assigned to mask use, 25 masks will be provided to each participant, one to be worn continuously (24/7), and then replaced every few hours (sooner if wet), for the 5 days at Mina.

The mask for this study is ‘3M™ Standard Tie-On Surgical Mask, Cat No: 1816’. Masks may be removed for eating, praying, washing, brushing teeth, or if the pilgrim experiences discomfort. Oral and written information about the instructions for correct mask wearing and disposal will be provided to the mask group (Appendix 2). Study staff will practically demonstrate the correct method of how to wear masks and help pilgrims to put on their mask for the first time. Masks can be changed every 4- 6 hours or more frequently if the masks become damp or damaged. Handouts will be distributed to all pilgrims at ‘mask tents’ to encourage correct mask wearing and explain the correct disposal of used masks. Small plastic bags will be provided for mask disposal and subjects will be instructed to discard the plastic bag containing used masks into waste bins provided for subsequent sanitary disposal. A subset of disused masks can be saved for further testing by multiplex viral PCR. A research team member will be available each morning and evening to distribute additional facemasks should pilgrims request extra, and to document any reported ILI symptoms development.

On recruitment, study staff will record each tent number, the number of people recruited and the total number of people in the tent. All pilgrims will be given a *Hajj health* diary (Appendix 3) for 5 nights at Mina (corresponding to 13-17 October, 2013, and 2-6 October, 2014). Each diary will have a unique barcode identifying the diaries with a specific study participant. The diaries will contain questions on demographics, medical conditions, and influenza vaccination history (Appendices 3 and 4). Each participant will provide information about the presence or absence of respiratory symptoms and fever in the diary every day whenever it is most convenient (eg after their evening meal). Pilgrims will also record in their diaries the amount of time they have worn the mask, the number of masks used per day and whether they were wearing one in their sleep.

No mask will be provided to anyone in the ‘no mask’ tents (although pilgrims may use their own supply of masks) but they will be enrolled in the study, informed consent will be obtained and the baseline questionnaire completed, then they will be given diaries to record their ILI symptoms and encouraged to record relevant information.

The *Hajj health* diaries will be collected on the 4th day evening from both ‘mask’ and ‘no mask’ groups when *post-Hajj health* diaries will be distributed to these pilgrims with self-addressed prepaid envelopes. Pilgrims will be instructed to post these diaries to the researchers. Pilgrims whose *Hajj health* diaries were not collected on the 4th day will be instructed to send thosealong with *post-Hajj health* dairies (Appendix 4) in the same envelope.

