**Specimen collection and testing**

In both groups of tents the study team members will actively search for pilgrims suffering from ILI (defined as subjective or measured fever and at least one respiratory symptom such as cough, sore throat and rhinorrhea) at least once every day. A study team member will collect nasopharyngeal (NP) swab (or throat swab if an NP swab is not doable) for molecular diagnostic testing for respiratory viruses. As a part of the routine care pilgrims in both tent groups will be supplied with generic medications (such as acetaminophen and ibuprofen) for fever or aches in addition to antiviral drugs for confirmed influenza patients.

The swabs will be stored within 2-3 hours at subzero temperature for later molecular diagnostic testing at the Centre for Infectious Diseases and Microbiology Laboratory Services (CIDMLS), Westmead Hospital, NSW, Australia. Pilgrims will provide their email addresses, phone numbers and mail addresses if they wish to receive the results of the laboratory test. Multiplex reverse transcriptase polymerase chain reaction (RT-PCR) for influenza A and B, MRES CoV and other corona viruses, parainfluenza viruses (types 1,2, 3 and 4), RSV A and B, adenoviruses, human metapneumovirus (hMPV), and picorna viruses will be performed. Nasal swabs will be taken for reverse transcriptase polymerase chain reaction (RT-PCR) analysis of respiratory virus infection. The swab used will be Copan nylon flocked dry nasal swab. The study staff who will take the swab will all have been trained to achieve an appropriate sample.

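### The protocol writes a morning and evening staff contact that records ILI into the mask tents only, which may raise case ascertainment there and bias the comparison toward no benefit

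*Protocol*

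**What the plan says.** The Data collection section describes the two arms in turn. The mask-arm paragraph opens "For the tents assigned to mask use, 25 masks will be provided to each participant", goes on to mask instructions and disposal, and ends by placing staff on hand, "available each morning and evening to distribute additional facemasks should pilgrims request extra, and to document any reported ILI symptoms development". The text on the no-mask tents covers consent and the baseline questionnaire, and adds "then they will be given diaries to record their ILI symptoms and encouraged to record relevant information". It mentions no morning or evening staff contact.

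The rule common to both arms is under Specimen collection and testing: "In both groups of tents the study team members will actively search for pilgrims suffering from ILI", with a frequency of "at least once every day". A team member takes the swab. Figure 2 shows swabbing of symptomatic pilgrims during the Mina stay; after Mina the protocol describes only diaries. The Recruitment section says participants are told their tent's allocation. The Data analysis section names both ILI and laboratory-confirmed virus as primary endpoints.

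**The concern.** PCR is objective, but it is done only on pilgrims who were found ill and swabbed. A case missed in Mina cannot be recovered later for the laboratory endpoint. If staff are on hand twice a day in mask tents with the task of recording ILI, while control tents are assured of one search a day, an ill pilgrim in a mask tent may have more chances of being found. The people making these contacts hand out masks, so they know the arm.

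More complete ascertainment in mask tents would raise the mask-arm count and dilute or hide a real benefit. The ILI endpoint is exposed too, so far as ILI recorded by staff counts toward it; the diaries themselves are kept in both arms. No later analysis can restore swabs that were never taken, so the matter belongs in the protocol.

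**Working it through.** **Inputs from the protocol (Sample size calculation).** Laboratory-confirmed infection 12% vs 6%, 80% power, 5% significance (taken as two-sided), ICC 0.10, 75 per tent, 2976 per arm before loss to follow-up.

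**Reproducing the stated figure.** Design effect = 1 + (75 − 1) × 0.10 = 8.4. Unpooled n = (1.960 + 0.842)² × (0.12 × 0.88 + 0.06 × 0.94) / 0.06² = 353.2, rounded up to 354; 354 × 8.4 = 2974. The pooled formula gives 356 × 8.4 = 2990. Both agree with 2976 to within rounding, so no figure in the protocol is wrong on this point. Effective n = 2976 / 8.4 = 354.3 per arm, with power 80% when ascertainment is complete.

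**Adding ascertainment (assumed).** Observed rate = true rate × proportion of cases found. If control tents get one contact a day and mask tents two, each contact finds an existing case with probability s, and the case is detectable for k days, then:

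- control: c = 1 − (1 − s)^k
- mask: m = 1 − (1 − s)^(2k)
- observed RR = 0.50 × m / c when the true RR is 0.50

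Power is for the two-sided test of 0.12c vs 0.06m at 354.3 per arm. The last column sets both arms at the control level c, so the gap between the last two columns is the loss due to unequal ascertainment alone.

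| s, k | control found | mask found | observed RR | power | power if both at c |
|---|---|---|---|---|---|
| 0.8, 3 days | 99.2% | about 100% | 0.504 | 78.7% | 79.5% |
| 0.8, 2 days | 96% | 99.8% | 0.52 | 74% | 78% |
| 0.5, 3 days | 87.5% | 98.4% | 0.56 | 61% | 74% |
| 0.8, 1 day | 80% | 96% | 0.60 | 48% | 70% |
| 0.5, 1 day | 50% | 75% | 0.75 | 14% | 49% |

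Assuming 95% vs 80% directly gives 0.057 vs 0.096, so RR = 0.59 and power is 50%, against 70% with 80% in both arms.

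**No true effect, 95% vs 80% found.** Observed rates are 0.12 × 0.95 = 0.114 (mask) and 0.12 × 0.80 = 0.096 (control), RR = 1.19. The difference is 0.018 and its standard error is √[(0.114 × 0.886 + 0.096 × 0.904) / 354.3] = 0.0230, a shift of 0.78 standard errors. The test then rejects in 12.2% of trials: 11.9% wrongly show harm from masks and 0.3% wrongly show benefit, where 2.5% each way is intended. In the three-day, s = 0.8 case total rejection stays at 5.0%.

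**The case against.** A reader might infer that cases *are* found more often in mask tents, by design. The documents do not support that:

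- The active search covers both arms, and its daily frequency is a minimum that may be exceeded in either.
- The morning and evening contact is passive. Staff are available, masks are given on request, and only reported symptoms are recorded. The text does not say that this contact leads to a swab, and it may coincide with one of the daily searches.
- Control tents are not expressly denied similar contact. The protocol supplies routine medications in both arms, so ill control pilgrims also have a reason to come forward.
- An illness lasting several days gets several daily searches, and the difference then nearly vanishes.

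All of this stands, and it reduces the point from an established bias to a risk. It does not remove the risk. A common minimum does not make the arms equal, and the only contact written beyond it is in the mask arm. ILI reported at resupply would meet the symptom condition for a swab. Late onsets within a five-day stay leave few further searches.

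A second tempting reading is that a 12% type I error threatens a false claim of efficacy. It does not: the excess rejections are almost all in the direction of harm, and false benefit becomes rarer. For an efficacy claim the bias is conservative, and what is mainly at risk is power and the size of the estimate.

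**Conclusion.** The concern holds as a risk created by the wording. As written, the protocol permits more intensive ILI ascertainment in mask tents for an endpoint that depends on symptomatic cases being found, in a trial whose participants know their arm. The likely direction is toward no benefit. The size cannot be fixed from the documents: a true risk ratio of 0.50 could be observed as practically 0.50, as about 0.60 with power near 50%, or as high as 0.75. These figures rest on assumed detection probabilities, on two contacts a day against one, and on the protocol's own rates, ICC and sample size. The text does not show that ascertainment will in fact differ. It fails to ensure that it will not, and the change needed is small enough that it should be made.

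**What to change.** In Data collection and in Specimen collection and testing, state one ILI ascertainment schedule, one script and one swab trigger for both arms; for example, hold the existing active search a fixed and equal number of times per day. Take ILI documentation out of the mask-resupply contact. State that, for study recording and swabbing, ILI mentioned at resupply is taken up at the next scheduled search, in the same way as in control tents. Deleting the documentation clause alone would not be enough, because the resupply contact would remain with no rule for what is mentioned there.

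Log staff contacts per tent. Report by arm the swabs per participant and the swabs per diary-reported ILI. The second is the more telling check, since a real mask effect would also lower swabs per participant.

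Cost: protocol and staff-instruction wording, brief logging and a small extra analysis. Fixing the search above once a day, or matching the resupply visits in control tents, may need more staff time. Some incidental contact at resupply will remain; the check would show whether it matters.

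### The Hajj diary is scheduled for five nights but collected on the evening of day 4, and Figure 2 starts the post-Hajj diary only on departure from Mina, so day 5 has no diary assigned for self-reported symptoms and mask use

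*Protocol*

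**What the plan says.** The relevant statements are in the Recruitment section (including Figure 2) and the Data collection section of the protocol.

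- **Diary period.** Every participant receives a Hajj "diary (Appendix 3) for 5 nights at Mina (corresponding to 13-17 October, 2013, and 2-6 October, 2014"). Symptoms and fever are to be entered "in the diary every day whenever it is most convenient (eg after their evening meal"). Time spent wearing a mask, the daily mask count and wear during sleep go into the same diary.
- **Day 1.** Staff approach tents "on the morning or afternoon of the first day of the pilgrim’s stay in Mina", dated 13 October 2013 and 2 October 2014.
- **Collection.** The "diaries will be collected on the 4th day evening from both" groups, and post-Hajj diaries are handed out at that moment. Figure 2 shows the same step for 2013: "Study staff collect *Hajj diaries* in the evening", listed between the labels for 16 and 17 October.
- **Start of the second diary.** Figure 2 reads "Pilgrims leave Mina and start keeping" post-Hajj diaries. The prose in Data collection gives no start date.
- **Exception.** Pilgrims whose Hajj diary was not collected on day 4 post it later with the post-Hajj diary.
- **Length of stay.** Background gives a stay in the tents of five days or more, and Data collection sets mask use over five days at Mina.

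**The concern.** The diary is the daily symptom record in both arms. It is also the only described source on how much the masks were worn. The Data analysis section counts effectiveness against ILI among the primary endpoints and lists diaries among its data sources. Background reports that the authors of the largest earlier study raised poor compliance with mask use as a concern, so adherence data matter for interpreting this trial.

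If the schedule is followed as written, the last scheduled diary day of the masking period is not recorded in either diary. The exception also makes observation time uneven: a pilgrim whom staff fail to reach on day 4 can contribute five days of self-report, while one who is reached contributes four at most. Follow-up length would then depend on the logistics of the collection round. An entry that was never made cannot be recovered by any later analysis plan.

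**Working it through.** **1. The plan's own diary length.** Counting inclusively, 13 to 17 October 2013 is 17 − 13 + 1 = 5 days, and 2 to 6 October 2014 is 6 − 2 + 1 = 5 days. The stated five nights reproduce in both years.

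**2. Where day 4 falls.** Day 1 is 13 October 2013 and 2 October 2014. Day 4 is therefore 13 + 3 = 16 October 2013 and 2 + 3 = 5 October 2014. Figure 2 agrees for 2013. Day 5 is 17 October 2013 and 6 October 2014.

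**3. Entries a diary collected on time can hold.** At most four of five. The missing share is 1/5 = 20% of that participant's scheduled diary days.

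**4. Whether the second diary covers the gap.** It is handed out on day 4, so participants hold a form on day 5. Figure 2, however, starts it on leaving Mina. Five nights at Mina that include 17 October place departure after the fifth night. On the plan's own count, the post-Hajj diary then begins too late for day 5. The departure date cannot be read from the flattened text of Figure 2. A later departure would widen the gap, hence at least one day.

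**5. Share of all scheduled diary days.** This is f × 1/5, where f is the fraction of diaries collected on time. The protocol does not give f, so a range is assumed:

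| f (assumed) | share of scheduled diary days without an assigned diary |
| --- | --- |
| 50% | 0.50 × 1/5 = 10% |
| 75% | 0.75 × 1/5 = 15% |
| 100% | 1.00 × 1/5 = 20% |

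**6. Which data are affected.**

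| Day-5 information | Source described | Affected by the day-4 collection? |
| --- | --- | --- |
| Laboratory-confirmed infection | Search for ILI at least daily, with swabbing, both arms (Specimen collection and testing) | No |
| Staff-detected or staff-documented ILI | The same search; team member present morning and evening to document reported ILI (Data collection) | No |
| Self-reported symptoms | Diary | Yes |
| Mask hours, mask count, wear during sleep | Diary | Yes; no other source described |

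**The case against.** Several points limit how far this goes.

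- **Outcome data.** A reader might infer that day-5 outcomes are lost. They are not lost as a class. The primary aim concerns laboratory-confirmed infection, which comes from staff search and swabbing, and nothing says these stop when the diaries are collected. This stands.
- **Most participants.** Collection on day 4 is the default, but no on-time share is given and missed diaries are posted later. How many participants are affected is unknown.
- **Power.** One could take the syndromic comparison at its minimum size (1170 / 1.18 ≈ 992 per arm, design effect 8.4) and multiply both rates by 4/5. That gives 24% versus 12% in place of 30% versus 15%, and nominal power falls from about 79% to about 67%. The documents do not support this as a consequence of the rule. It requires the diary to be the only source, every diary to be collected on day 4, onsets to be even over exactly five days, and no day-5 illness to persist into the post-Hajj entries. The sample size section gives the 30% without a time window.
- **Dilution.** The same calculation keeps the relative reduction at 50%, so it shows no dilution of the effect.
- **Day 4 as well.** Evening collection could pre-empt an entry made after the evening meal, but the meal is only an example of a convenient time. Loss of the day-4 entry is possible, not established.
- **Bias.** The rule applies to both arms alike, so no between-arm bias follows from it.
- **Forms not visible.** Appendices 3 and 4 are in a supplement that was not available. A look-back item in the post-Hajj diary, or an earlier printed start date, cannot be ruled out.

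These points narrow the consequence. They do not remove the conflict over the diary period, the collection day and the start of the second diary.

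**Conclusion.** The contradiction holds, in limited form. A five-night diary collected on the fourth evening, followed by a diary that Figure 2 starts only on departure, leaves at least day 5 with no diary assigned. For each diary collected on schedule that is one of five entries. Over the whole trial it is 10% to 20% of scheduled diary days if 50% to 100% are collected on time (assumed). The cost is completeness of self-reported symptoms, of mask-use data in particular, and unequal observation time between pilgrims collected on time and those missed.

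The conclusion rests on reading Figure 2's start of the post-Hajj diary literally and on the unseen form having no look-back item. The documents do not support a claim of lost laboratory or staff-detected outcomes, of bias between arms, or of a particular loss of power. The change is still worth making, because it costs almost nothing and the missing entries could not be restored later.

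**What to change.** Make the two diaries contiguous, in one of two ways:

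1. Start the post-Hajj diary when the Hajj diary is collected (16 October 2013; 5 October 2014), with the mask-use items carried over for the remaining days at Mina.
2. Collect the Hajj diary after its fifth entry (17 October 2013; 6 October 2014, or later).

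Then align the Data collection text, Figure 2 and both diary forms for both years, so that diary period, collection time and start of the post-Hajj diary agree. Under option 1, also state whether the collection-day entry belongs to the first or the second diary, so that it is neither missed nor recorded twice.

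Option 1 costs a date change and a few added items on the form. Option 2 costs a later collection round. Neither needs more participants or any additional study procedure.
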